## Abstract

**Background:**

Community violence is a persistent and challenging public health problem. Community violence not only physically affects individuals, but also its effects reverberate to the well-being of families and entire communities. Being exposed to and experiencing violence are adverse community experiences that affect the well-being and health trajectories of both children and adults. In the United States, community violence has historically been addressed through a lens of law enforcement and policing; the impact of this approach on communities has been detrimental and often ignores the strengths and experiences of community members. As such, community-centered approaches to address violence are needed, yet the process to design, implement, and evaluate these approaches is complex. Alternatives to policing responses are increasingly being implemented. However, evidence and implementation guidance for community-level public health approaches remain limited. This study protocol seeks to address community violence through a resilience framework—Adverse Community Experiences and Resilience (ACE|R)—being implemented in a major US city and leveraging a strategy of community organizing to advance community violence prevention.

**Objective:**

The objective of this research is to understand the impact of community-level violence prevention interventions. Furthermore, we aim to describe the strategies of implementation and identify barriers to and facilitators of the approach.

**Methods:**

This study uses a hybrid type 1 effectiveness-implementation design. Part 1 of the study will assess the effectiveness of the ACE|R framework plus community organizing by measuring impacts on violence- and health-related outcomes. To do so, we plan to collect quantitative data on homicides, fatal and nonfatal shootings, hospital visits due to nonaccidental injuries, calls for service, and other violence-related data. In Part 2 of the study, to assess the implementation of ACE|R plus community organizing, we will collect process data on community engagement events, deliver community trainings on community leadership and organizing, and conduct focus groups with key partners about violence and violence prevention programs in Milwaukee.

**Results:**

This project received funding on September 1, 2020. Prospective study data collection began in the fall of 2021 and will continue through the end of 2023. Data analysis is currently underway, and the first results are expected to be submitted for publication in 2024.

**Conclusions:**

Community violence is a public health problem in need of community-centered solutions. Interventions that center community and leverage community organizing show promise in decreasing violence and increasing the well-being of community members. Methods to identify the impact of community-level interventions continue to evolve. Analysis of outcomes beyond violence-specific outcomes, including norms and community beliefs, may help better inform the short-term and proximal impacts of these community-driven approaches. Furthermore, hybrid implementation-effectiveness trials allow for the inevitable contextualization required to disseminate community interventions where communities drive the adaptations and decision-making.

**International Registered Report Identifier (IRRID):**

DERR1-10.2196/50444

## Introduction

Community violence is a persistent problem impacting public health. Community violence impacts the overall mental and physical health of neighborhoods, towns, and collective spaces. Risk factors associated with violence and community trauma include community poverty, community disadvantage, and disorganization [1]. Research framed through social disorganization theory, sometimes referred to as “broken windows theory,” has suggested that disorder within a community can impact mental health and contribute to stress in individuals [2]. Among youths and adolescents, the impacts of community violence are particularly strong [3]. Violence, including experiencing physical violence and being a witness to violence, is considered an adverse childhood experience that can significantly impact children’s future physical and behavioral health [4]. Different types of violence against youths, such as child abuse and neglect and community youth violence, often share the same risk and protective factors [5].

Protective factors, contrasted with risk factors, are increasingly seen as key to effective community-level violence prevention interventions. In taking a strength-based approach, which highlights protective factors, there is an opportunity to center the role of community members and their experiences while moving away from risk-framing approaches [6]. Strength-based approaches to community violence prevention are those that consider community relationships as a positive, protective factor against violence. Resilience theories, along with constructs of collective efficacy and social cohesion, have allowed for an expanded understanding of how to consider structural-level interventions leveraging protective factors to address community violence [7].

Interventions conducted at the community level can impact multiple individuals, particularly youths, at once [8]. Community-level interventions can interrupt patterns of violence at the structural level, preventing exposure to violence at an early age, and can move beyond school-based approaches commonly targeting youth [9]. Furthermore, community-level interventions developed through an asset-based framework, rather than deficits, have gained wider understanding and evidence. One community-level primary prevention strategy that has been explored in the context of community resilience is community organizing [10]. Community organizing can be defined as a process in which people affected by common concerns aim to build their power together and identify solutions for those shared concerns by mobilizing [11,12]. Community organizing, in the context of community violence prevention, seeks to address issues of social cohesion and isolation by building up relationships within communities and having communities lead the violence prevention strategies. Community organizing has been incorporated into interventions seeking to address domestic violence [13], as well as a way to empower youth in the violence prevention space [14,15].

It is difficult to implement community-level interventions and measure their effects, because of the complexity of intermingled contextual and temporal factors. Community-level interventions are often not broadly disseminated nor scaled up because they are developed according to the unique demographic characteristics of the community, as well as the unique characteristics of the practitioners or other persons leading implementation. Community-level interventions may also occur at a particular moment in time that cannot be easily incorporated into statistical models to determine intervention impacts. Hybrid trials seek to address these problems by allowing for implementation-related data collection to be incorporated into the study design [16]. Thus, this study uses a hybrid type 1 implementation-effectiveness trial; these are typically conducted early in the intervention development process and have the primary aim of evaluating the effectiveness of an intervention while allowing for the collection of implementation-related data to improve dissemination and intervention uptake.

Adding to the complexity of researching community-based interventions is the appropriate selection of statistical approaches to analyze community-level outcomes captured as interrupted time series data. Statistical decisions include the choice of analytic model (eg, autoregressive integrated moving average vs regression), if and how to account for autocorrelation and seasonality, if and how to correct for a small sample size, and aligning the statistical strategy with the available data, such as the number of time points. Reporting the planned analytic strategy a priori in protocol papers is important for avoiding bias due to a selected approach, as well as engendering confidence in the results [17].

Promising structural interventions that account for these methodological and implementation issues to address community violence have emerged in recent research. Cure Violence, a violence prevention intervention adapted from “Chicago Ceasefire” that was developed in the mid-1990s, framed violence as a communicable disease [18]. Through adaptations and implementations in multiple cities over the last 3 decades, the impacts of Cure Violence have been mixed [19]. The research has allowed for an evolved understanding of the importance of changing community norms around violence, in addition to the physical acts of violence [20,21]. Another study building on Chicago Ceasefire, the CeaseFire 365 intervention, effectively reduced gun violence in Baltimore while identifying the importance of measuring nonviolence-related outcomes to determine impact. The intervention included weekend “ceasefires” in which community events and public meetings sought to communicate a stop to violence during specific times [22].

Building on previous experiences and challenges of Cure Violence and similar community violence prevention interventions, the Prevention Institute (PI) and the University of California San Francisco, developed the Adverse Community Experiences and Resilience (ACE|R) framework as a community-level approach to violence prevention. The ACE|R framework uses community-specific data combined with an underlying evidence-based understanding of how adverse childhood experiences impact adolescents and communities [10]. In 2016, PI introduced the ACE|R framework to over 150 community partners and residents in Milwaukee during a time when the Milwaukee Blueprint for Peace—a call to action for violence prevention—was in development. The PI partnered with the Milwaukee Office of Violence Prevention (OVP) to facilitate the development of the Milwaukee Blueprint for Peace using the ACE|R framework, including having residents identify the leading risk and resilience factors related to violence in Milwaukee. These factors were solicited through community conversations, roundtable discussions, and web-based surveys. Residents and community organizations shared input on the emerging vision and principles in alignment with the ACE|R framework through those same forums. Through this citywide organizing and mobilization approach to comprehensive planning, a shared set of goals, strategies, and indicators was identified and formally launched in 2017 as the Blueprint for Peace.

The primary objective of this study is to assess whether community organizing and mobilizing residents to act on the Blueprint for Peace increases the effectiveness of the ACE|R framework to reduce community-level measures of child abuse and neglect and youth violence in 4 select communities, compared with having no community organizing in the 6 remaining select communities. The secondary objective is to explore the barriers to and facilitators of implementing community organizing as a strategy for increasing support for the sustainability of the Blueprint for Peace and the reduction of community-level violence in Milwaukee.

## Methods

### Study Design

To meet the objectives of this study, the proposed research design is a hybrid type 1 effectiveness-implementation design using a mixed methods approach, leveraging both quantitative and qualitative methods to measure the effect of the ACE|R plus community organizing on communities and collect data on the implementation of community organizing. We present the details of the proposed study in two parts: part 1 describes the proposed study to measure the effectiveness of the ACE|R plus community organizing, and part 2 describes how we will measure the implementation of the ACE|R plus community organizing.

### Setting

This proposed study will take place in Milwaukee, Wisconsin, where the Blueprint for Peace was first launched in 2017. Blueprint for Peace participants in the development process selected 10 communities as the neighborhoods to prioritize and focus on violence prevention efforts (Figure 1). This study focuses on 4 of the 10 selected communities, hereafter referred to as the “select communities.”

**Figure 1 figure1:**
[figure not shown]
Map of Milwaukee, with the 10 communities where the Blueprint for Peace Initiative has been implemented highlighted in blue.

### Intervention—Blueprint for Peace and the Resident Leadership and Advocacy Training

The proposed study uses the ACE|R framework plus community organizing as a strategy to directly address the need for community-level action to prevent child abuse and neglect and youth violence. Intervention communities will receive training and technical assistance that integrates the ACE|R framework, community organizing and mobilization, and operational knowledge of the Milwaukee Blueprint for Peace**.** The goal of this intervention element is to prepare residents and other interested parties in the community (eg, community-based organizations and faith-based organizations) to understand and be prepared to act on (organize or support) structural community-level change in support of the Blueprint for Peace. The ACE|R plus community organizing trainings (hereafter referred to as “resident leadership and advocacy training”) consist of 5 modules that ground participants in the knowledge of systemic trauma and then cover ways to address neighborhood violence through community-designed solutions. The details of each of the training modules are presented in Table 1.

**Table 1 table1:** Content details for the 5 modules that make up the resident leadership and advocacy training.

Module	Module title	Module objective	Example content
1	Systematic and Historical Trauma (Adverse Community Experiences and Resilience)	Learn about systematic and historical trauma through the recognition that the impact is cumulative and reverberates across neighborhoods for generations	Defines adverse childhood experiences Defines trauma
2	Social Determinants of Health and THRIVE^a^	Explore community factors—people, places, and equitable opportunities—that influence health, safety, and well-being in their neighborhoods	Defines the social determinants of health inequities and describes how socioeconomic factors and neighborhood characteristics shape behaviors Identifies strategies to address community-level factors and move toward health equity Discusses the role of neighborhood, home, and work environments in determining health and the quality of life
3	Addressing and Preventing Community Trauma and Healing	Learn ways to address community trauma through healing	Healing as a starting point for community and system transformation, including activities to explore opportunities for healing and identify strong examples of how community healing is already taking place in the neighborhood Strategies for healing Strategies to address community trauma
4	Building Resident Leadership and Voice, Navigating Systems from Civic Engagement to Movement Building	Identify the steps of effective community action, including needs and issue assessment and strategic planning	Defines key components of a toolkit specific to Milwaukee city and county processes Outlines opportunities for shifting power by elevating community ownership, creating community change, such as shifting policy, and influencing decision makers. An overview of the Blueprint for Peace and the goal areas, including discussion and activities, to map how it is connected to existing neighborhood efforts and neighborhood goals that support the blueprint
5	Resident Leadership in Action—Needs and Opportunity Assessment	Identify actions they will take to implement community action	Readiness assessment designed to guide and support communities in determining capacity-building needs Readiness assessment to build a plan for community mobilization of assets that accelerates community-level violence norms change and collective action toward a public health approach to violence prevention

^a^THRIVE: Tool for Health & Resilience in Vulnerable Environments.

### Part 1: Effectiveness of the ACE|R Framework Plus Community Organizing

To define and determine the effect of a community violence prevention intervention, the first part of this study will be an effectiveness study of the ACE|R framework plus community organizing. This part will include using an idiographic clinical trial research design that captures within-community changes to analyze the Blueprint for Peace–related activities and outcomes, including child abuse and neglect, youth violence, and other violence-related outcomes (Textbox 1).

Key measures to evaluate the implementation and effectiveness of Adverse Community Experiences and Resilience (ACE|R) plus community organizing through outcome constructs.
**Outcome constructs and tracked measures**
Increased community organizingEvents led by individuals trained in community organizingLong-term development of safe and healthy communitiesHomicidesNonfatal shootings in select neighborhoodsFatal shootings in select neighborhoodsFirearm-related injuriesArrests due to violence among youths younger than 18 yearsArrests due to child maltreatmentCalls for service in selected communitiesNuisance, vacant, and blighted properties abated in select neighborhoodsPoverty rate in select neighborhoodsReduced adverse childhood experiencesChildren hospitalized for confirmed and suspected child abuse or violence-related injuryChildren at the emergency department for confirmed and suspected child abuse or violence-related injuryHome removalsReduced child abuse and neglectChild protective services referralsChild maltreatment reportsRate of child victims per 1000 childrenIncreased social cohesionBlock clubs in select neighborhoodsResident-led events in select neighborhoodsIncreased awareness of violence prevention strategiesNeighborhood perceptions of safety, resilience, and access to resources and servicesAwareness of neighborhood assets, resources, and programming among neighborhood residents

### Data Analysis

Primary analysis of outcome measures will use intensive hierarchical modeling with maximum likelihood estimation, a multilevel linear model that has evolved for use in small-sample clinical trials [24]. This approach can capitalize on both change from baseline (preintervention) to treatment phases of time series data and differences between communities that do and do not receive an intervention.

Recent developments in intensive hierarchical modeling for small samples allow for evaluation models that (1) control for biases due to small samples, (2) estimate intervention impacts that are quantified in terms of phase “jumps” and slopes, (3) use thorough power analysis using Monte Carlo simulation, and (4) have the ability to model and test complex causal inferences [24,25]. For intensive hierarchical modeling of the ACE|R plus community organizing impacts, time series data are clustered within communities; the effect of community organizing is quantified at level 1 as change over time, with aggregate models across communities being analyzed at level 2. Corrections to statistical testing and parameter estimates (to account for small sample sizes) will include the Satterthwaite degrees of freedom [26] and use full information maximum likelihood estimation for statistical testing of parameters but estimate model parameters using restricted maximum likelihood.

Differences between baseline and treatment phases will be estimated within the 4 select communities; community-level factors that may enhance or attenuate the impact of resident leadership and advocacy training will be explored using between-select communities fixed effects. An additional contrast will be to compare the changes in the 10 select communities to matched communities in Milwaukee outside the study.

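### The primary objective compares 4 organizing communities with the other 6, but the analysis commits to no 4-versus-6 contrast, and its one explicit comparison group sits outside all 10

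*Protocol article*

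**What the plan says.** **Objective.** The last paragraph of the Introduction asks whether organizing and "mobilizing residents to act on the Blueprint for Peace increases the effectiveness of the ACE|R framework" "in 4 select communities, compared with having no community organizing in the 6 remaining select communities". This is a concurrent comparison of two groups of communities. Its target is what organizing adds to the framework.

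**Communities.** The Setting section says that participants in developing the Blueprint "selected 10 communities as the neighborhoods to prioritize and focus on violence prevention efforts". The Figure 1 caption reads "Map of Milwaukee, with the 10 communities where the Blueprint for Peace Initiative has been implemented highlighted in blue". All 10 are therefore Blueprint communities, and 4 of them also receive organizing.

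**Analysis.** The last paragraph of Data Analysis lists three pieces of work:

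1. "Differences between baseline and treatment phases will be estimated within the 4 select communities".
2. Community factors that may strengthen or weaken the training's impact "will be explored using between-select communities fixed effects".
3. "An additional contrast will be to compare the changes in the 10 select communities to matched communities in Milwaukee outside the study".

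**Terminology.** In Setting, "This study focuses on 4 of the 10 selected communities, hereafter referred to as the" 'select communities', which makes the term mean 4. The Introduction speaks of 4 select and 6 remaining select communities. The last paragraph of Data Analysis uses the term once for 4 and once for 10, and Recruitment uses it for 10.

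**The concern.** None of the three planned pieces is the comparison named in the primary objective. The 6 communities that the Introduction makes the comparison group never appear as one in the analysis. The only comparison group named there lies outside all 10, and the contrast against it counts the 6 as treated.

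Two things are at stake. First, a before-after change in the 4 cannot be separated from whatever else changed in Milwaukee over the same period. The Discussion itself describes pandemic-related disruption to staffing, recruitment and possibly to the work of the Office of Violence Prevention. Second, a reader looking for controlled evidence on organizing will find only the 10-versus-outside result. That result could be near zero when organizing works, or clearly positive when organizing adds nothing and the Blueprint does the work in all 10.

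**Working it through.** The article states no effect size or power figure on this point, so there is nothing to reproduce. The check is what each planned analysis estimates.

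**Inputs from the article.** There are 4 communities with organizing and 6 without (Introduction). The Blueprint is in place in all 10 (Figure 1 caption). Spillover into control communities is possible, with no size given (Discussion, Expected Findings).

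**Notation (assumed).** For the change in an outcome from baseline to treatment phase, as jump or slope:

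- T = change common to the whole city
- B = further change shared by the 10 Blueprint communities
- O = effect of organizing
- s = fraction of O that spills over to the 6
- w = weight of the 4 within the 10

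Expected change:

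- outside areas: T
- the 6: T + B + s·O
- the 4: T + B + O

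**What each analysis estimates.**

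| Analysis | Estimates | Isolates O? |
|---|---|---|
| Within the 4 (planned) | T + B + O | No: T and B remain |
| 10 versus outside (planned) | B + [w + (1 − w)s]·O | No: B remains, O is scaled down |
| 4 versus 6 (objective, not planned) | (1 − s)·O | Yes, apart from spillover |

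The last row assumes that T and B are the same in the 4 and the 6. Communities are not randomized, so this is an assumption.

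**Coefficient on O in the 10-versus-outside contrast.**

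- Equal weights, no spillover: w = 4/10, s = 0, coefficient 0.40.
- Unequal weights, s = 0: w from 0.25 to 0.60 gives 0.25 to 0.60.
- Spillover at w = 0.4: s = 0.10 gives 0.4 + 0.6 × 0.10 = 0.46; s = 0.25 gives 0.55; s = 0.50 gives 0.70.

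**Effect of the shared change B** (w = 0.4, s = 0), with the contrast as a multiple of O:

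| B/O | 10 versus outside | 4 versus 6 |
|---|---|---|
| −0.5 | −0.5 + 0.4 = −0.1 | 1.0 |
| 0 | 0.4 | 1.0 |
| 0.5 | 0.5 + 0.4 = 0.9 | 1.0 |
| 1 | 1 + 0.4 = 1.4 | 1.0 |

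If O = 0, the contrast equals B. The more basic fault is therefore the mixing with B: the result can fall below or exceed the organizing effect, and nothing in the contrast shows which.

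**Do the exploratory fixed effects fill the gap?** Under the Setting definition, 'between select communities' means among the 4, all of which have organizing. Under the wider use it could span all 10, but the stated purpose is still to find factors that modify the training's impact. Neither reading commits to organizing versus none.

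**The case against.** The case on the other side has five parts.

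- **The pooled contrast is only additional.** This is correct. The primary analysis quantifies organizing as change over time within communities, and the design description takes control and treatment data from the same community. A reader might infer that the trial's main estimate of organizing is diluted to 40%. The article does not support that: the within-4 estimate uses organizing communities only and is not diluted. Its weakness is the lack of a concurrent control.
- **Comparing all 10 with outside areas is a sensible question.** This also stands. All 10 have the Blueprint, so for a Blueprint-wide question the 6 are properly treated units and the contrast need not be dropped. But the article does not label it that way, and it appears in a section whose modelling is introduced as being about organizing.
- **A 4-versus-6 comparison was in view.** Data Analysis remarks that the approach can use differences between communities with and without an intervention, and the Discussion mentions control communities. The first describes what the method can do, and neither names a contrast.
- **A condensed article leaves model terms to the full plan.** This is true of detail such as covariance structure. Here the article does name its contrasts, and those named do not match its stated primary objective. It also argues in the Introduction that the analytic strategy should be reported in advance.
- **The 10 may be a slip for 4.** If so, the scaling of O disappears, but B still remains in the contrast and 4 versus 6 is still absent.

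It is also tempting to attach a loss of power to the pooled contrast. The article gives no standard deviation, effect size, significance level or number of matched communities, so no such figure is supportable.

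**Conclusion.** The point holds as a mismatch between objective and analysis. The primary objective is 4 versus 6; the analysis commits to uncontrolled change in the 4, exploratory moderators, and 10 versus matched outside areas. The plan as written never tests its stated primary objective. Its one explicit comparison with other areas estimates B + 0.40·O with equal weights and no spillover; the coefficient is 0.25 to 0.60 for other weights and 0.46 to 0.70 for spillover of 10% to 50% at a weight of 0.4. The 0.40 is derived here and would be the whole story only if B were also zero. The conclusion that organizing is not isolated does not depend on any of these values. The double use of 'select communities' is a further defect that makes the mismatch hard to see.

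**What to change.** 1. In Data Analysis, state the 4-versus-6 difference in phase jump and phase slope as the test of the primary objective, fitted as phase-by-organizing interactions in the multilevel model with data from all 10 communities. For the 6, use the same calendar change point as for the 4.
2. Keep the comparison of the 10 with matched outside communities, but label it an evaluation of the Blueprint overall. Optionally split it into 4 versus outside (Blueprint plus organizing) and 6 versus outside (Blueprint alone). State that no conclusion on organizing will be drawn from the pooled contrast.
3. Describe the within-4 phase change as an uncontrolled before-after estimate.
4. Use 'select communities' for one set only, for example 'Blueprint communities' for the 10, 'organizing communities' for the 4 and 'comparison communities' for the 6.
5. The Results section says that analysis is under way, so date the statement and say whether outcomes by group had been seen.

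**Cost.** Wording and a few extra model terms, with the same outcome series needed for the 6, which the 10-versus-outside contrast already requires. The real price is precision. Treating each community as one change score, the standard error of a 4-versus-6 difference is √(1/4 + 1/6) = 0.645 of the between-community standard deviation of change, so intervals will be wide and should be reported as such. Spillover would shrink the estimate by the factor (1 − s), which should be stated as a limitation.
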